##### Early Detection Cohort

We propose a cluster randomized study to be implemented at 18 HIV treatment facilities in Lusaka province. Three facilities serving each type of regional population (urban, periurban, or rural populations) will be randomly assigned to a study arm: the ARROW program or one-time education. Overall, 9 (50%) facilities will be assigned to each arm of the trial, with data collection at baseline and at 12-, 24-, and 36-month follow-up. At each of the 18 clinics, we will enroll 100 men and 100 females resulting in a total of 3600 participants in the early detection cohort. The 200 AYA living with HIV per facility will be selected by first reviewing the HIV register and identifying those who meet the study inclusion criteria: 15 to 39 years of age, on ART for at least 6 months, not pregnant, and with no pending plans to move from the current residence during the 3-year study duration. For all the 3600 participants, we will collect baseline data and capture information on study end points from the SmartCare system, and the supplemental data will be collected by PCs and trained study data collectors (eg, tracking referrals for all participants and obtaining results of biopsies).

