**HIV status, demographics, mediating outcomes, intervention dose, and clinical services**				
	HIV status and diagnosis date	Perinatally or behaviorally infected; CD4 count	Clinic record	Baseline
	Demographics and socioeconomic status	Research Triangle Institute AYA Zambia survey	Self-report	Baseline
	Self-efficacy (AYA living with HIV)	Generalized self-efficacy Scale [69]	Self-report	Baseline and 12, 24, and 36 mo
	Social support and mental health (AYA living with HIV)	Brief social support and patient health questionnaires [69,70]	Self-report	Baseline and 12, 24, and 36 mo
	HIV and cancer stigma (AYA living with HIV)	Anticipated stigma measures [71,72]	Self-report	Baseline and 12, 24, and 36 mo
	Cancer risk (AYA living with HIV)	Updated Research Triangle Institute cancer survey	Self-report	Baseline and 12, 24, and 36 mo
	Group education and sessions (AYA living with HIV)	Number and proportion of education sessions attended (dose)	PC tool; study database	12, 24, and 36 mo
	One-on-one education (AYA living with HIV)	Number of women receiving each level of strategy (dose)	PC tool; study database	12, 24, and 36 mo
	HIV and cancer team training (health care provider)	Proportion who attended initial training sessions (dose)	PC tool; study database	12, 24, and 36 mo
	Network meetings (health care provider)	Number and proportion of meetings attended (dose)	PC tool; study database	12, 24, and 36 mo
	Clinical team knowledge, confidence in ability, and collaboration (health care providers)	Survey on skills and patient communication; stigma related to AYA living with HIV (modified Nyblade instrument [73]) and peer learning and coordination	Self-report	Baseline and annually
	Diagnostic procedures by cancer type	Number of supplemental and diagnostic tests conducted	Clinical record	12, 24, and 36 mo
	Treatment modality by cancer type	Chemotherapy sessions; surgery; type of radiation	Clinical record	12, 24, and 36 mo

^a^KS: Kaposi sarcoma.

^b^NHL: non-Hodgkin lymphoma.

^c^CC: cervical cancer.

^d^PC: peer counselor.

^e^CD4: cluster of differentiation 4.

^f^Among AYA living with HIV and diagnosed with cancer.

^g^NHL stage based on the Lugano classification, CC stage based on the International Federation of Gynecology and Obstetrics, and KS stage based on the AIDS Clinical Trial Group system.

^h^AYA: adolescents and young adults.

^i^ART: antiretroviral therapy.

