### Analysis of Hypotheses

We will use an intent-to-treat approach to test the hypotheses (related to the dual primary and secondary end points) that AYA living HIV in the ARROW program, compared with those receiving one-time education, will have higher uptake of early diagnostic services, increased adherence to treatment, and improved outcomes.

For the facilities assigned to the intervention group in the early detection cohort, we will examine the effects at the individual level across the 2 randomization groups. Given the need to consider the influence of the cluster randomization, we will use generalized estimating equation models to estimate the effect across the trial arms. If the Hausman assumption of correlation between the random and fixed effects is violated, then we will include fixed effects representing cluster identification [74]. For the cancer treatment cohort, we will generate summary statistics for the end points and test statistical significance. We will also conduct logistic regressions to identify key factors that predict adherence.

For both trials, we will adjust for baseline covariates, including sociodemographic factors, should the initial descriptive analyses suggest differences in the distribution of these factors across the study arms. We will also explore the use of propensity scores to control for systematic differences between the AYA living with HIV in the 2 trial arms. In further analyses, we will compare differences in mediating outcomes across the randomized groups and examine the potential moderating roles of key individual behavioral and social factors hypothesized to influence adherence along the cancer care continuum (eg, social support, stigma, and self-efficacy), as shown in Figure 1. We will test the “dose” of the ARROW program received as a covariate in these models. In additional analysis, we will explore differences in the end points by age groups and type of cancer, as appropriate. We will also assess whether knowledge, self-efficacy, social support, and stigma differ by age groups and among AYA living HIV, both with and without cancer.

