For measures where we have baseline and 12-, 24-, and 36-month data (eg, self-efficacy and stigma), we will perform difference-in-difference analysis, which will allow for comparisons over time and across the study arms. To understand potential variation across the HIV treatment facilities, we will conduct comparisons to analyze differences in mediating outcomes for the AYA living with HIV and the study end points. Furthermore, to understand ARROW program’s impact on health care providers, we will assess dose of the intervention (network session attendance) and change in knowledge, confidence in ability to care for AYA living with HIV, and peer collaboration.

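### Difference-in-difference for self-efficacy, stigma and similar measures is valid but usually less precise than adjusting for the collected baseline; in the 18-facility cohort the adjustment must include the facility mean

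*Protocol article*

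**What the plan says.** The section Analysis of Hypotheses in the protocol article takes the measures with a baseline and three annual follow-ups, naming self-efficacy and stigma as examples, and states that "we will perform difference-in-difference analysis, which will allow for comparisons over time and across the study arms". Table 2 confirms that the baseline exists: self-efficacy, social support and mental health, HIV and cancer stigma, and cancer risk are all timed at "Baseline and 12, 24, and 36 mo".

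The same section gives these measures a supporting role: "In further analyses, we will compare differences in mediating outcomes across the randomized groups". Covariate adjustment is conditional: "we will adjust for baseline covariates, including sociodemographic factors, should the initial descriptive analyses suggest differences". The outcome's own baseline value is not named as a covariate.

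The two trials randomise different units. For the early detection cohort, "We propose a cluster randomized study to be implemented at 18 HIV treatment facilities in Lusaka province", with 9 facilities per arm and 200 participants planned in each. For the cancer treatment cohort, individual patients are allocated within cancer type, 250 per arm (Sample Size and Recruitment).

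**The concern.** A difference-in-difference contrast subtracts the whole baseline difference between arms, which fixes the coefficient on baseline at one. When units are randomised there is no systematic baseline difference to remove, so the coefficient can instead be estimated. With independent units the estimated coefficient gives the same expected effect with a variance that is no larger, apart from a small cost of estimating it.

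The baseline is also only partly persistent. If the arms differ at baseline by chance, difference-in-difference removes the full difference although only a fraction r is expected to carry over. Given that imbalance, the estimate is shifted by (1 − r) times the difference; at r = 0.5 that is half of it. The Limitations section itself notes that cluster randomisation raises the risk of baseline differences between arms.

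At stake is the width of the intervals for the comparisons of mediating outcomes by arm, on which the framework of Figure 1 draws.

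**Working it through.** The article gives no standard deviation, baseline-to-follow-up correlation or power for these scales, so there is no planned figure to reproduce. All correlations below are assumptions.

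**Cancer treatment cohort (individual randomisation, one follow-up).** In units of the outcome variance, with r the baseline-to-follow-up correlation:

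- follow-up alone: 1
- difference-in-difference: 2(1 − r)
- baseline-adjusted: 1 − r²
- adjusted ÷ difference-in-difference: (1 − r²) / [2(1 − r)] = (1 + r)/2

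| r | Difference-in-difference | Adjusted | Ratio |
|---|---|---|---|
| 0.3 | 1.40 | 0.91 | 0.65 |
| 0.5 | 1.00 | 0.75 | 0.75 |
| 0.7 | 0.60 | 0.51 | 0.85 |
| 0.9 | 0.20 | 0.19 | 0.95 |

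At r = 0.5 the interval is 1 − √0.75 = 13% narrower. Below r = 0.5, difference-in-difference has a larger variance than ignoring baseline altogether. Estimating the slope with 500 patients costs a factor of 1 + 1/496, about 0.2%. If the three follow-ups are averaged and all visits are equally correlated, the ratio becomes (1 + 3r)/4, or 0.63 at r = 0.5.

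**Early detection cohort (9 v 9 facilities).** Inputs:

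- m = 180 per facility: 200 planned, less the 10% attrition in Sample Size and Recruitment.
- ICC 0.03–0.05: stated there for the binary end points and assumed here for the scales.
- π, the correlation of facility effects over time, and τ, the individual correlation: assumed.

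Variance of one facility mean:

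- difference-in-difference: 2·ICC·(1 − π) + 2(1 − ICC)(1 − τ)/m
- adjusted for individual baseline only, slope τ: ICC·(1 − 2τπ + τ²) + (1 − ICC)(1 − τ²)/m
- adjusted for the facility-mean baseline: [ICC + (1 − ICC)/m]·(1 − R²)·(1 + 1/14), where R = [ICC·π + (1 − ICC)τ/m] / [ICC + (1 − ICC)/m] and 1 + 1/14 is the cost of estimating a slope from 18 facilities.

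Worked case: ICC 0.05, π = 0.9, τ = 0.5.

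- Difference-in-difference: 0.01000 + 0.00528 = 0.01528.
- Individual baseline only: 0.01750 + 0.00396 = 0.02146, which is 1.40 times as large.
- Facility mean: R = 0.862, and 0.05528 × (1 − 0.862²) × 15/14 = 0.01524, which is about equal.

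Adjusted ÷ difference-in-difference at τ = 0.5 (ICC 0.03 / 0.05; above 1 favours difference-in-difference):

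| π | Individual baseline only | With facility mean |
|---|---|---|
| 0.5 | 0.75 / 0.75 | 0.80 / 0.80 |
| 0.7 | 0.88 / 0.89 | 0.89 / 0.90 |
| 0.8 | 1.01 / 1.05 | 0.94 / 0.95 |
| 0.9 | 1.28 / 1.40 | 0.99 / 1.00 |
| 0.95 | 1.55 / 1.84 | 1.01 / 1.02 |

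At π = 0.95, τ = 0.7 and ICC 0.05 the facility-mean ratio is 1.03. A simulation with 4,000 replicates per setting, estimating the slopes, gave the same pattern. At π = 0.9 and τ = 0.5 the ratios were 1.30 / 1.34 with the individual baseline only and 1.01 / 0.99 with the facility mean.

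The reason is that a single slope, set mainly by variation within facilities, is too shallow for the stable differences between facilities. A separate facility-mean term lets the between-facility slope differ.

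**The case against.** The strongest objection is that the textbook efficiency result is for independently randomised units, while most participants are in the cluster trial: 3442 enrolled there against 105 in the cancer cohort at the time of the article. This stands. With 180 per facility, individual variation makes up only about 10–15% of the variance of a facility mean (0.95/180 = 0.0053 beside 0.05; 0.97/180 = 0.0054 beside 0.03). The ratio (1 + r)/2 therefore cannot be carried over to that trial.

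Second, difference-in-difference is a legitimate analysis of a randomised trial, and comparing change is an understandable response to the baseline differences the authors expect. This also stands: the shift from chance imbalance is conditional on that imbalance and averages to zero over randomisations.

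Third, one sentence in an article may not fix the estimator, and a repeated-measures model with arm-by-visit terms is often given the same name. This does not remove the point. If the arms have their own baseline means, that model gives the same change-score contrast with complete data. Only a version constraining the arms to a common baseline mean would recover the gain, and the article does not describe one.

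Fourth, the correlations are unknown. That is correct, and at r = 0.9 the gain in the cancer cohort is only 5%.

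**Conclusion.** The point holds as a minor matter of efficiency. In the cancer treatment cohort, adjusting for the baseline is at least as precise as difference-in-difference apart from a cost of about 0.2%. The variance is 35%, 25%, 15% or 5% lower at assumed r of 0.3, 0.5, 0.7 or 0.9. In the early detection cohort the result depends on how stable facility means are and on how baseline enters the model. With the facility mean included, it runs from about 20% less variance (π = τ = 0.5) to about equal, or 1–3% more when facility means are very stable.

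A reader might infer that baseline adjustment is never worse under randomisation, that it has no downside, or that 15–35% is available across the whole trial. The figures do not support this for 18 facilities. Nor do they support reading the planned analysis as biased or invalid.

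The cluster figures assume that the end-point ICC applies to the scales and that all 180 per facility are surveyed. If only about 28 per facility were followed (an assumption from the 250 per arm under Implementation Outcomes, 250/9), individual-baseline adjustment alone would have ratios of about 0.90–0.98 at π = 0.9, τ = 0.5, and 1.04 at π = 0.95, ICC 0.05.

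Only supporting mediating outcomes are affected. No primary or secondary end point and no stated power depends on this.

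**What to change.** Prespecify, for every measure with a baseline and regardless of observed imbalance, one repeated-measures model of the 12-, 24- and 36-month values on arm, visit, arm by visit and the participant's baseline value. In the early detection cohort add the facility-mean baseline and the urban, periurban or rural stratum, with clustering by facility and small-sample inference. Keep difference-in-difference as a sensitivity analysis.

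The cost is a change of wording, best made before any comparison by arm is run; no new data are needed. The downside is a possible loss of a few percent in precision in the cluster cohort if facility means are very stable. The two stratum terms raise the slope-estimation factor from 1 + 1/14 to 1 + 1/12, about 1% more.

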### Implementation Outcomes

For assessing the ARROW program, we will collect measures (as outlined in Table 3) from those receiving and implementing ARROW: 250 selected AYA living with HIV with follow-up data collection at the HIV treatment clinics and 250 AYA living with HIV at the Cancer Diseases Hospital, 36 HIV care providers, 12 oncology staff from the Cancer Diseases Hospital, 10 Health Care Collaborative members, and all the PCs. We will collect similar measures focused on the education campaign from those receiving the brochures in the one-time education campaign arm: 250 AYA living with HIV in the early detection cohort, 250 AYA living with HIV in the cancer treatment cohort, and 36 HIV care providers.

**Table 3 table3:** Implementation outcomes measurement.

Constructs	Measures	Stakeholder and data	Frequency
Acceptability, feasibility, and appropriateness	AIM^a^, FIM^b^, and IAM^c^ 4-item measures	AYA^d^ living with HIV, PCs^e^, and health care provider (HIV and cancer) surveys	12-, 24-, and 36-mo follow-up
Fidelity (group and one-on-one education, health care provider meetings, and education campaign)	All content is delivered, or brochures are provided; meetings take place at the frequency and sequence planned	PC tracking tools, the ARROW Provider Network, and the Health Care Collaborative meeting minutes	12, 24, and 36 mo
Sustainability	SMSS^f^ subscales specific to strategies	PCs, health care providers, and administrators	12 and 36 mo

^a^AIM: Acceptability of Intervention Measure.

^b^FIM: Feasibility of Intervention Measure.

^c^IAM: Intervention Appropriateness Measure.

^d^AYA: adolescents and young adults.

^e^PC: peer counselor.

^f^SMSS: Sustainment Measurement System Scale.

Our measurement will include the 4-item questions from the Acceptability of Intervention Measure, the Feasibility of Intervention Measure, and the Intervention Appropriateness Measure [75]. Fidelity will be assessed using data collected in the PC tracking tool and Network meeting. The fidelity measures described in Table 3 will be compiled annually, and summary statistics (eg, proportion of sessions in which all content was delivered) will be generated to assess compliance with study protocols. Sustainability will be assessed using subscales of the Sustainment Measurement System Scale [76]. We will review the scores and fidelity measures and compare scores available for both the ARROW and one-time education arms to assess implementation success and draw lessons to improve and optimize the ARROW program.

We plan to conduct interviews and focus groups to identify the underlying moderating factors associated with the successful implementation of strategies, along with facilitators and barriers to inform future scale-up activities. At 12 months, trained data collectors will interview PCs and health care providers as described for the quantitative measures. We will interview this group to seek feedback on their level of preparedness to implement the strategies, their assessment of the quality of the delivery, the level of responsiveness of the AYA living with HIV, whether they felt there were facilitators to deliver the strategies and potential barriers, and suggestions to address the barriers. We will also interview the AYA living with HIV to seek feedback on the ARROW program and one-time education campaign.

At 36 months, at the end of the trials, we will conduct focus groups with PCs, AYA living with HIV, HIV care providers, and oncology care providers. These focus groups (7-10 participants) will explore topics related to the sustainability of the ARROW program and the one-time education campaign, drawing on the findings from the results of the Sustainment Measurement System Scale survey. We will critically discuss interpretations of the data until they reach a consensus on the dominant themes and meanings. The findings will offer insights to improve the ARROW program and understand perceptions of the one-time education campaign.

### Cost-Effectiveness and Return-on-Investment Scenarios

We will assess the incremental cost-effectiveness of the ARROW program compared with the one-time education campaign. As shown in Table 4, we will generate the cost of start-up activities to understand the resources required to plan future implementation, the activity-based cost of strategies during the intervention trials, and the estimated cost during scale-up. We will use a previously validated instrument, the Cost Assessment Tool, to collect resource use and cost information [77].

**Table 4 table4:** Cost data collection and analysis by phase.

Phase and data category		Purpose	Data elements (examples)
**Before implementation**			
	Start-up costs	To assess the cost of planning to implement strategies	Formalizing plans for the intervention; hiring staff; conducting training, readiness assessment, and strengthening processes
**Intervention implementation (randomized controlled trials)**			
	Implementation of activity-based cost data	To assess the cost of implementing and maintaining interventions	Implementation activities: delivering strategies, tracking outcomes, quality assurance, data collection, and evaluation Patient cost: travel cost and time lost from work
	Resource use	To standardize cost	Labor hours (peer counselors and project staff) and nonlabor resources
**Future expansion**			
	Scale-up cost	To estimate the cost of large-scale implementation	Fixed versus variable activity-based cost estimates of implementation strategies to project economies of scale

Our main goal is to estimate the implementation cost from the program perspective. We will estimate labor hours by prospectively tracking time spent by each project staff member, including PCs, on a predefined set of activities (individuals will report their time monthly) and use hourly wages to calculate cost. We will capture time spent by health care providers, administrators, and policy makers participating in the ARROW Network and Collaborative using from the meetings. We will also document the expenditures on nonlabor resources to produce education materials, hosting group education sessions, the ARROW Provider Network meetings, and the cost of providing travel support. Using activity-based costing, we will allocate separate costs for supporting early diagnosis services and treatment adherence.

On the basis of these cost estimates and the primary end points from the trial, we will conduct incremental cost-effectiveness analysis by generating the cost per AYA living with HIV undergoing early detection services (physical examinations for KS and NHL and screening for CC) and the cost per AYA living with HIV and cancer completing recommended treatment modalities. Using standard economics methodology, we will explore economies of scale related to the implementation costs that can be achieved during scale-up [77,78]. We will also assess the key drivers of the cost of the ARROW program.

Using the trial data on estimated shift in stage at diagnosis and treatment adherence rates, along with supplemental information on prevalence of KS, NHL, and CC and mortality by stage at diagnosis, we will estimate the projected difference in mortality between ARROW and one-time education for AYA living HIV in Zambia. For CC screening, we will also estimate the incremental change in mortality using a validated microsimulation model, as screening not only will identify CC at an early stage but also can prevent CC by treating precancerous lesions [79,80].

We will derive the cost per life year saved (for all the 3 cancers combined), and our estimates will include both direct and indirect costs (patient time loss). The latter represents the opportunity cost of engaging in health services. We will assess whether the derived costs per life year saved are cost-effective or considered acceptable for implementation based on cost-effectiveness profiles of other strategies or interventions already implemented [81]. The estimated cost and effectiveness will be used to assess return on investment based on resources required to implement the ARROW program and the economic burden that will be reduced by avoiding premature mortality and treatments for adverse events related to KS, NHL, and CC for AYA living with HIV.

Furthermore, we will conduct policy simulations to assess the impact of scaling up ARROW and perform a sensitivity analysis, varying the range of effectiveness and cost estimates, and generate potential best- and worst-case projections. We will create tornado and spider diagrams to display this uncertainty graphically to policy makers. This cost-effectiveness analysis will be complemented by a budget analysis, which will identify the financial outlays that will be required annually to implement the ARROW program at scale.

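### As worded, the return on investment credits avoided treatment but charges only ARROW's implementation resources, leaving out the screening, diagnostic and treatment services that ARROW is designed to generate

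*Protocol article*

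**What the plan says.** The protocol article's section Cost-Effectiveness and Return-on-Investment Scenarios sets out the costing as follows.

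- **Perspective.** "Our main goal is to estimate the implementation cost from the program perspective".
- **Labour.** Hours come from "prospectively tracking time spent by each project staff member, including PCs, on a predefined set of activities", valued at hourly wages. For clinicians and officials the text adds: "We will capture time spent by health care providers, administrators, and policy makers participating in the ARROW Network and Collaborative". It names no clinical service time.
- **Nonlabour.** The team will "document the expenditures on nonlabor resources to produce education materials, hosting group education sessions", and will also record Network meetings and travel support.
- **Table 4.** The resource-use row lists "Labor hours (peer counselors and project staff) and nonlabor resources". Another row adds patients' travel cost and lost work time. The column is labelled as giving examples.
- **Cost per life year saved.** This is for the three cancers combined and takes in direct and indirect costs. Indirect cost is explained as patient time; direct cost is not explained.
- **Return on investment.** It rests on "resources required to implement the ARROW program and the economic burden that will be reduced by avoiding premature mortality and treatments for adverse events".

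Table 2 separately records clinical volumes, among them "Number of supplemental and diagnostic tests conducted" and treatment modality by cancer type. The costing text does not say that these volumes will be priced.

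**The concern.** ARROW is meant to work by raising the use of services: more cervical screening, more completed diagnostic work-up, more treatment started and finished. Those services cost the health system money. The Introduction describes care as free of charge, so patient-reported costs cannot stand in for that expense.

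If the return on investment credits the treatment and deaths that ARROW avoids but charges only the cost of running ARROW, its two sides have different scopes. The added services produce the credited benefit, yet their cost appears on neither side. The results are intended for policy makers, who would set ARROW's cost per life year beside that of other interventions. That comparison needs a defined cost scope.

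**Working it through.** **Step 1. Is there a figure to reproduce?** No. The article gives no cost, cost-effectiveness ratio, return on investment or unit cost. The check is therefore a comparison of what is credited with what is charged, followed by the service volumes implied by the planned effects.

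**Step 2. Credits against charges, as described.**

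| Item | Credited? | Named as a cost? |
|---|---|---|
| Cervical screening | Yes, through the microsimulation of mortality | No |
| Precancer treatment | Yes, named as a route to preventing cervical cancer | No |
| Diagnostic tests | Yes, through the shift in stage at diagnosis | No |
| Added cancer treatment | Yes, through adherence in the mortality projection | No |
| KS/NHL physical examination | Yes, through stage shift | Partly: peer counselors examine (section Individual Level) and their time is tracked |
| Avoided treatment of adverse events | Yes, in the return on investment only | Not applicable |

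**Step 3. Added volume at the planned effects.** Inputs come from Overall Study Design and Sample Size and Recruitment: 1,800 participants per arm, of whom 900 are women; 15% against 35% examined; 20% against 40% screened; 250 cancer patients per arm; 75% against 90% adherent.

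- Extra women up to date with screening: 0.20 × 900 = 180, or 162 with 10% attrition.
- Extra people examined: 0.20 × 1,800 = 360, or 324 with 10% attrition. Part of this is already charged through peer counselor time.
- Extra treatment completers: 0.15 × 250 = 37.5.

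The numbers of follow-on diagnostic tests and precancer treatments cannot be computed from the article.

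**Step 4. How much could the omission matter?** Let P be the incremental cost per eligible ARROW participant under the listed inputs, and c the service cost per extra person served. Neither is given, so the ratio c/P is assumed. With a 20-point gain and no offset for avoided care:

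- incremental cost per participant is P as listed and P + 0.20c when complete;
- the share left out is 0.20c / (P + 0.20c) = c / (5P + c);
- a benefit-to-cost ratio is overstated by the factor (P + 0.20c) / P = 1 + 0.20c/P.

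| Assumed c/P | Cost understated by | Benefit-to-cost ratio overstated by |
|---|---|---|
| 0.1 | 2.0% | 2% |
| 0.25 | 4.8% | 5% |
| 0.5 | 9.1% | 10% |
| 1 | 16.7% | 20% |
| 2 | 28.6% | 40% |

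The middle column would also apply to the cost per life year, but only if its direct costs turn out to be the listed inputs and nothing more.

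**The case against.** The best defence is that a condensed article has been read too literally. Table 4 offers examples, and full cost inputs and unit-cost sources normally sit in a longer document. The programme perspective is stated for the implementation cost and is not said to govern the later ratios. Direct costs in the cost per life year could well include services. Table 2 collects most of the volumes needed, and a sensitivity analysis on costs and effects is planned.

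Much of this stands, and it rules out several stronger readings that a reader might infer:

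- *Both ratios credit avoided treatment.* The article states that credit for the return on investment only.
- *All the added examinations go uncharged.* Peer counselors do KS/NHL examinations and their hours are costed. Charging all 360 again could double count.
- *ARROW is shown to look cheaper than it is.* The stated credit is for treating adverse events, which does not clearly include avoided late-stage cancer treatment. If that saving is also unpriced, the net direction for treatment costs is unknown.
- *A dollar amount can be put on the omission.* No unit cost is given, so any such amount would be assumed.
- *The scale-up budget is distorted.* That analysis concerns outlays to implement ARROW, for which programme costs are the right scope.

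The defence does not cover the return-on-investment sentence. That sentence is not silent: it names implementation resources as the cost side and avoided treatment as part of the benefit side. A sensitivity analysis that varies the listed costs does not add a missing category.

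**Conclusion.** The concern holds for the return on investment as worded. Its cost side is narrower than its benefit side, and the services left out are ones ARROW is built to increase: cervical screening, diagnostic tests, precancer treatment and cancer treatment. Following the sentence as written risks a result that favours ARROW.

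For the cost per life year the point is weaker. Direct costs are undefined while only programme and patient inputs are described, so the scope is unclear rather than wrong.

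The volumes involved are not trivial (about 180 extra women up to date with screening and 37.5 extra treatment completers at the planned effects), but the size of the bias cannot be derived from the article. The 2% to 29% understatement of cost rests on assumed cost ratios of 0.1 to 2, the planned 20-point gain, and no offset for avoided care. It is an illustration, not an estimate.

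**What to change.** For the return on investment and the cost per life year:

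1. Define direct costs to include health-system service costs in both arms: volumes from Table 2 (screens, supplemental and diagnostic tests, treatment modality, and clinician examinations not already in tracked peer counselor time) multiplied by local unit costs, net of avoided care. Table 2 has no separate row for precancer treatment, so confirm that the clinical records supply that count.
2. State a health-system or societal perspective for these two ratios.
3. Keep the programme perspective for the cost per person served and for the budget analysis.

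The cost is obtaining local unit costs and some extra analysis; no new patients, staff or study procedures are needed. The Results section says the cost-effectiveness analysis is still to be conducted, so the change can be made in advance. The drawback for the sponsor is that the figures may become less favourable to ARROW.
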